### Participants

FEP patients who are cannabis users and meet the inclusion criteria (listed below) are to be included and randomly assigned to one of the two treatment groups. The sample size calculation was performed using data published in the literature related to the main theme of the study (Bonsack et al., 2011 [31]; Edwards et al., 2006 [32]; Hjorthøj et al., 2012; Madigan et al., 2013 [34]) and using Ene 2.0 software. To achieve a power of 80% to detect differences from the null hypothesis, H0: *μ*1 = *μ*2, using a bilateral Student’s *t* test for two independent samples, with a significance level of 5%, we need to include 30 patients in the experimental group and 30 patients in the control group, meaning a total of 60 patients for the study.

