#### Randomization

Patients are to be randomly assigned to one of the two treatment groups by permuted block randomization with a block size of 4 and a 1:1 allocation using a computer-generated random sequence. The allocation sequence will be prepared by an independent person not otherwise involved in the trial.

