### Assessment

Data collection is to be based on an assessment protocol for gathering data on sociodemographic, clinical and cannabis/other substance use-related variables. All patients are to be assessed at baseline, post-treatment and in the follow-up period (at 3 and 6 months and 1 year of follow-up from the end of the treatment program) (Table 2).

**Table 2 Tab2:** Assessment protocol

Assessments	Pre-treatment	Post-treatment	Follow-up^a^		
Sociodemographic variables	X				
Cannabis/other substance use-related variables					
Use	X	X	X	X	X
Severity	X	X	X	X	X
Clinical variables					
Diagnosis	X	X	X	X	X
Clinical severity	X	X	X	X	X
Illness awareness	X	X	X	X	X
Medication adherence	X	X	X	X	X
Clinical symptomatology	X	X	X	X	X
Psychosocial functioning	X	X	X	X	X
Biological variables					
Peripheral blood mononuclear cells	X	X	X	X	X
Toxins in urine	X	X	X	X	X

^a^Follow-up: 3 and 6 months and 1 year of follow-up from the end of the intervention program

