#### Statistical analysis

IBM SPSS version 23 will be used for the statistical analysis. The sociodemographic characteristics of the patients will be analyzed using descriptive statistics. Differences between the two intervention groups (cognitive behavioral therapy versus psychoeducation) will be analyzed using the χ^2^ test (or Fisher’s test where *n* ≤5) for categorical variables and the Student’s *t* test or Mann-Whitney *U* test (depending on the distribution of the data) for continuous variables.

The differences in cannabis use reduction between two intervention groups will be analyzed using Student’s *t* test and/or the Mann-Whitney *U* test and mixed models. Effect sizes will be calculated for differences in cannabis abstinence based on Cohen’s *d* or *r* [60] for Student’s *t* test and the Mann-Whitney *U* test, respectively. The results will be interpreted as small if *d* values are between .2 and .49, medium if *d* values are between .5 and .79, and large if *d* values are higher than .8.

Differences in efficacy between the interventions in terms of clinical and functional outcomes of patients will be analyzed with repeated measures models (baseline, post-treatment, 3 and 6 months and 1 year of follow-up) and logistic regressions.

Furthermore, whether cannabis abstinence is associated with better clinical and functional outcomes will be analyzed using linear regression models for continuous dependent variables, and Poisson regression models for categorical dependent variables.

Finally, the biological data of patients will be studied in conjunction with clinical data using multivariate analyses. Specifically, the possible alterations in the components of the ECS and the influence of the specific cognitive behavioral therapy program for cannabis cessation on the normalization of ECS will be analyzed using repeated measures models, mixed models or analysis of covariance. Further, the relation between normalization of elements of the ECS and improvement in symptoms and psychosocial functioning, attributable to the specific treatment, will be assessed by regression models.

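### Make baseline-adjusted use the main analysis of cannabis reduction: the planned t and Mann-Whitney tests name no baseline covariate, and adjusting is a near-free gain in precision

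*Protocol article*

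**What the plan says.** All of this is in the protocol article.

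- **Statistical analysis, cannabis use.** "The differences in cannabis use reduction between two intervention groups will be analyzed using" Student's t and/or Mann-Whitney tests together with mixed models. Effect sizes (Cohen's d or r) are tied to the t and Mann-Whitney tests. No baseline covariate is named, the mixed model's treatment of baseline is not described, and the three methods are not ranked.
- **Statistical analysis, endocannabinoid markers.** Here the options are "repeated measures models, mixed models or analysis of covariance". This is the only place where analysis of covariance appears.
- **Participants.** The trial is sized on a bilateral Student's t "test for two independent samples, with a significance level of 5"%. For 80% power, "we need to include 30 patients in the experimental group and 30 patients in the control group". No difference, SD or correlation is given.
- **Assessment.** "All patients are to be assessed at baseline, post-treatment and in the follow-up period". Table 2 marks both use and severity of use before treatment.
- **Abstract and objectives.** The primary outcome is cessation at post-treatment. The first specific objective is a greater reduction in use.

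**The concern.** Reduction most naturally means change from baseline. A two-sample test on change subtracts the whole baseline value from each patient's post-treatment value. That is the most precise use of baseline only when the regression slope of post-treatment on baseline is exactly 1. At any other slope, a model that estimates the slope does better. The sizing and the effect measures both rest on the two-sample tests, so one of these could well be the result that is read as decisive.

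What is at stake is precision. The trial has 60 patients, and the discussion names sample size as a limitation and expects difficulty with completion and attendance. The information needed for a better estimate is already being collected.

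**Working it through.** **The article's own figure.** The 30 per arm cannot be derived forward, because no difference or SD is stated. Solving backwards for 80% power, two-sided 5%, 30 per arm gives a standardised difference of d = 0.736 (noncentral t, 58 df) or 0.723 (normal approximation). The article does not say whether that d refers to the change or to the post-treatment score.

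**Inputs.** From the article: 30 per arm, 1:1, two-sided 5%, 80% power. Assumed, because the article gives no value: r, the correlation of baseline and post-treatment use, at 0.3, 0.5 and 0.7; and k = SD at baseline / SD at post-treatment, at 1, 0.7 and 0.5. A k below 1 is plausible: entry restricts EUROP-ASI severity to 4–9, while post-treatment scores can fall to 0.

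**Formulas**, in units of the post-treatment variance:

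- post-treatment value alone: 1
- change score: 1 + k² − 2rk
- baseline-adjusted (ANCOVA): 1 − r²
- change minus ANCOVA: (1 + k² − 2rk) − (1 − r²) = (k − r)², which is never negative
- ratio ANCOVA / change: (1 − r²) / (1 + k² − 2rk)

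The two methods tie when r = k. The change score is noisier than ignoring baseline when r < k/2, that is r < 0.5 at k = 1 and r < 0.25 at k = 0.5.

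**Variance ratio**

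| k | r = 0.3 | r = 0.5 | r = 0.7 |
|---|---|---|---|
| 1 | 0.91/1.40 = 0.65 | 0.75/1.00 = 0.75 | 0.51/0.60 = 0.85 |
| 0.7 | 0.91/1.07 = 0.85 | 0.75/0.79 = 0.95 | 0.51/0.51 = 1.00 |
| 0.5 | 0.91/0.95 = 0.96 | 0.75/0.75 = 1.00 | 0.51/0.55 = 0.93 |

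**Same result as sample size.** Dividing 30 by the ratio gives the arm size at which a change-score test would match ANCOVA on 30. At k = 1 it is 30/0.65 = 46, 30/0.75 = 40 and 30/0.85 = 35. At k = 0.5 it is 30/0.958 = 31, 30/1.00 = 30 and 30/0.927 = 32.

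**Same result as power.** Suppose the test on reduction really has its planned 80%. The effect for ANCOVA is then 0.736/√ratio, with 57 df. At k = 1, power is 93.5%, 89.9% and 85.9% for r = 0.3, 0.5 and 0.7. At k = 0.5 it is 81.6%, 80.0% and 82.9%.

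**Cost of adjusting.** One degree of freedom moves power from 80.00% to 79.98%. Chance imbalance in the covariate inflates the variance on average by 1 + 1/(60 − 4) = 1.018, about 2%; the ratios and powers above leave this out. In simulation (8,000 trials per scenario, k = 1, r from 0 to 0.7), type I error of ANCOVA was 4.7–5.4%.

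**The case against.** Four points on the other side carry weight.

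- **Mixed models are already named.** A reader who stops at the t and Mann-Whitney tests might infer that they are the only planned analyses and that the key outcome gets the least efficient method. The article does not support that: the same sentence adds mixed models, and one with baseline as covariate would recover the gain. What stands is that the article leaves open how baseline enters and which analysis governs.
- **The gain may be small.** A reader might infer that a change score over-corrects whenever r is below 1, and that a 15–35% cut in variance is assured. Both need equal SDs at baseline and post-treatment. Under the range restriction imposed by the entry criteria, the gain can nearly vanish.
- **Nothing is invalid.** Under randomisation the unadjusted tests are unbiased and hold their type I error, and chance imbalance is already reflected in their standard error. Mann-Whitney is also a defensible choice for skewed use data with many zeros. This stands in full.
- **Covariates belong in the analysis plan.** An article often leaves the model form to a plan that is not shown here. That excuses the undescribed mixed model. It does not fully cover the choice of lead method, since the article itself states the unadjusted tests, ties the effect sizes to them and sizes the trial on a two-sample t test.

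**Conclusion.** The point holds as an improvement in precision, not as the correction of an error. For continuous cannabis measures, a baseline-adjusted analysis is at least as precise as a test on change for every r and k, apart from one degree of freedom and about 2% variance inflation at N = 60.

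The size of the gain cannot be fixed from the article. It is substantial if the SDs are equal and r is modest, and close to nil if the baseline SD is half the post-treatment SD. The power figures rest further on the assumption that the planned 80% applies to the change score.

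Two stronger conclusions should not be drawn. The planned tests do not bias the comparison. And none of these variance or power figures carries over to cessation as a yes/no outcome, which is how the abstract's primary outcome may be read.

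**What to change.** In the statistical analysis section, or in the analysis plan, state for each continuous use measure (EUROP-ASI, CUPIT, frequency and dose):

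- The main analysis is a model for the post-treatment value with arm and the baseline value of the same measure as covariates. This may be ANCOVA, or the mixed model already named with baseline as covariate; say which one leads.
- Standard errors are robust or bootstrapped if the measure is skewed.
- The adjusted difference with its confidence interval is the headline result. The t and Mann-Whitney tests and their effect sizes are supportive.

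Analyse yes/no cessation separately, without citing the gain above. The change costs wording only. Baseline values are already scheduled for all patients, and no patients, visits or assays are added. Recruitment was still open when the article was submitted, so the choice could be fixed before the data are analysed.

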The limitations of this study are mostly related to typical limitations of this type of clinical trial with a longitudinal design, in particular, the sample size. Another limitation is that this type of patient with a dual diagnosis often has a lack of illness awareness, and poor insight and treatment adherence, and hence there may be difficulties in completion of the program and attendance to follow-up visits by participants. These factors should be taken into consideration in interpreting the efficacy of the therapy and the impact of intervention on the clinical and functional outcomes of patients.

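### The 60-patient size makes no allowance for the loss the protocol expects, and the model named for clinical and functional outcomes may discard patients who miss one visit

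*Protocol article*

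**What the plan says.** **Size (Participants).** The aim is stated as "To achieve a power of 80% to detect differences from the null hypothesis" of equal means, with a two-sided t test at the 5% level. For this, "we need to include 30 patients in the experimental group and 30 patients in the control group". The sentence then closes with the overall number for both arms, "meaning a total of 60 patients for the study". No difference, standard deviation, standardized effect or loss rate is given.

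**Expected loss (Discussion, limitations paragraph).** Because patients with a dual diagnosis often have poor insight and poor adherence, "there may be difficulties in completion of the program and attendance to follow-up visits by participants". The only response is that this be kept in mind when results are interpreted.

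**Analysis (Statistical analysis).** Three sets of methods are named:

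- Cannabis use reduction: t test and/or Mann-Whitney U test, and mixed models. None is ranked first.
- Clinical and functional outcomes: "Differences in efficacy between the interventions in terms of clinical and functional outcomes of patients will be analyzed with repeated measures models" covering baseline, post-treatment, 3 months, 6 months and 1 year, plus logistic regressions. Mixed models are not mentioned.
- Biological data, for the effect of the program on the endocannabinoid system: "repeated measures models, mixed models or analysis of covariance".

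The Abstract places the primary comparison, cannabis cessation, at post-treatment.

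**The concern.** Two statements in the same article do not fit together. One fixes enrolment at exactly the number the power calculation requires. The other says that some of those patients may not complete or attend. Every patient not assessed at post-treatment is lost to the t test on which the trial was sized, so the stated power is a best case presented as the planning value.

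The second problem is one of wording with a practical consequence. For the biological data the plan treats repeated measures models and mixed models as different things. For the clinical and functional outcomes it names only the former. In SPSS, the software the plan names, the classical repeated-measures analysis of variance keeps only patients with a value at every visit, whereas a mixed model uses whatever visits exist. With five visits over more than a year in this population, that choice could decide whether a large share of the sample is analysed.

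**Working it through.** **1. The plan's own figure.** Inputs from Participants: two-sided 5%, power 80%, 30 per arm. The effect size is not stated, so 30 per arm cannot be reproduced independently. It can only be back-solved:

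- Normal approximation: d = (z₀.₉₇₅ + z₀.₈₀) × √(2/30) = (1.960 + 0.842) × 0.258 = 0.723.
- Noncentral t with 58 degrees of freedom: d = 0.736.

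Feeding either value back into the standard two-means formula returns 30 per arm. This is circular and confirms only that the inputs are coherent.

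**2. Power if only assessed patients enter the t test.** Let m be the number assessed per arm. Power is the probability that a noncentral t variable with 2m − 2 degrees of freedom and noncentrality d√(m/2) exceeds the two-sided 5% critical value. With d = 0.736, and loss rates that are assumptions because the article gives none:

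| Assumed loss | m per arm | Noncentrality | Power |
|---|---|---|---|
| 0% | 30 | 2.85 | 80% |
| 10% | 27 | 2.70 | 76% |
| 20% | 24 | 2.55 | 70% |
| 30% | 21 | 2.38 | 64% |

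At 24 per arm, the difference detectable with 80% power rises from 0.736 to 0.826.

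**3. Enrolment that would keep 30 assessed per arm.** Using 30/(1 − loss), rounded up:

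- 10% loss: 30/0.9 = 33.3, so 34 per arm, 68 in total.
- 20% loss: 30/0.8 = 37.5, so 38 per arm, 76 in total.
- 30% loss: 30/0.7 = 42.9, so 43 per arm, 86 in total.

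**4. Patients kept if the five-visit model deletes listwise.** Assume baseline is complete and the same fraction is missing at each of the four later visits.

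- 10% missing per visit, independent across visits: 60 × 0.9⁴ = 39.4, about 39 kept.
- 15% missing per visit, independent: 60 × 0.85⁴ = 31.3, about 31 kept.
- 10% missing per visit, always the same patients: 60 × 0.9 = 54 kept.

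Real attendance would probably lie between the independent and the fully overlapping case, so 39 to 54 is the relevant range at 10%.

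**5. Does loss imply a known direction of bias?** Assume true abstinence of 30% in both arms and that everyone lost is still using.

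- Loss 30% experimental, 10% control: 0.30/0.70 = 43% against 0.30/0.90 = 33%, an apparent gain of about 10 points.
- Losses reversed: 33% against 43%, an apparent harm of the same size.
- Equal loss of 20%: 0.30/0.80 = 37.5% in both arms, no difference.

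The sign depends entirely on which arm loses more patients, and the article does not say.

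**The case against.** **Mixed models are already in the plan.** This is correct for cannabis use reduction. A reader might infer that every named test uses complete data only; the Statistical analysis section does not support that. What remains there is that the mixed model has no stated priority. The article ties its effect sizes to the t and Mann-Whitney tests, both of which omit anyone absent at post-treatment.

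**The term repeated measures models is not tied to a procedure.** This is also fair: it can cover a mixed model, and listwise deletion is an inference. The inference has some basis, because the biological sentence lists the two as alternatives, but the wording is ambiguous rather than plainly wrong. The deletion figures are therefore conditional.

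**The limitation is disclosed.** The Discussion acknowledges both sample size and attendance. Disclosure does not change the power statement, which is still made without qualification.

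**The effect size is unknown.** The value 0.736 is back-solved, and an allowance could in principle be hidden inside the calculation. Nothing in the text suggests one: the number needed and the number to include are the same.

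**A tempting stronger reading** is that the protocol foresees dropout among continuing users and hence a cessation result biased towards the experimental arm. The Discussion speaks of insight, adherence and attendance. It does not mention differential loss by arm or a direction, and step 5 shows that the sign can go either way.

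**Missing-data detail belongs in an analysis plan.** That is accepted. The absence from an article of an analysis-population rule or of a rule for missing urine tests is not part of this point.

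**Conclusion.** The point holds in two parts.

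First, the stated 80% power is true only with complete post-treatment data, while the article itself expects incomplete attendance. Under the back-solved effect, the shortfall is about 4, 10 and 16 percentage points at losses of 10%, 20% and 30%. These figures rest on the t test, on an effect of about 0.74 that the article does not state, and on assumed loss rates.

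Second, the model for clinical and functional outcomes is named in a way that permits an analysis dropping anyone who misses one visit. If that procedure were used, about 39 of 60 patients would remain at 10% independent missingness per visit, and more if the same patients miss repeatedly.

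The article does not support the conclusion that the cessation analysis is confined to completers, or that its result is biased in a known direction. This point should be corrected, but it does not invalidate the design.

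**What to change.** - **Participants:** say that 30 per arm gives 80% power only if all 60 patients are assessed at post-treatment, and add the power at a stated assumed loss (for example, about 70% at 20%), together with the effect size used. Raising enrolment to the totals in step 3 is an alternative, but a costly one; recruitment was still open at submission, according to Trial status.
- **Statistical analysis, clinical and functional scales:** replace the general term with a linear mixed model using all randomised patients and every available visit, adjusted for the baseline value.
- **Statistical analysis, cannabis use reduction:** give the mixed model already named priority over the t and Mann-Whitney tests.
- **Sensitivity analysis:** counting absent patients as still using is suitable here only. If absence is unrelated to use and true abstinence is 30% in both arms, loss of 10% in the experimental arm and 30% in the control arm gives 0.30 × 0.90 = 27% against 0.30 × 0.70 = 21%, a spurious 6-point benefit.

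**Cost:** a less favourable stated power, some rewording, and a different procedure in the same software. A mixed model gains little from a patient with no post-baseline value. It also does not remove bias if patients are absent because they are still using, which is why the sensitivity analysis is needed.

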**Methods/design:**

This is a single-blind randomized study with 1 year of follow-up. Patients are to be randomly assigned to one of two treatments: (1) specific cognitive behavioral therapy for cannabis cessation composed of 1-hour sessions once a week for 16 weeks, in addition to pharmacological treatment scheduled by the psychiatrist, or (2) a control group (psychoeducation + pharmacological treatment) following the same format as the experimental group. Participants in both groups will be evaluated at baseline (pre-treatment), at 16 weeks (post-treatment), and at 3 and 6 months and 1 year of follow-up. The primary outcome will be that patients in the experimental group will have greater cannabis cessation than patients in the control group at post-treatment. The secondary outcome will be that the experimental group will have better clinical and functional outcomes than the control group.

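### Clinical and functional outcomes: baseline is modelled as one of five outcome levels, with no baseline adjustment and no named contrast for objective 2, which dilutes the group effect and can cost power

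*Protocol article*

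**What the plan says.** Objective 2, at the end of the Background, asks whether the cannabis programme leads to better symptoms and functioning than standard treatment at follow-up. The Abstract makes this the secondary outcome: "The secondary outcome will be that the experimental group will have better clinical and functional outcomes than the control group".

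The Statistical analysis section says that these outcomes "will be analyzed with repeated measures models (baseline, post-treatment, 3 and 6 months and 1 year of follow-up) and logistic regressions". The bracket lists the levels of the repeated factor, and baseline is the first of five. The section does not say which term of the model answers objective 2 (group, group-by-time or a visit contrast), and it gives no baseline adjustment for these outcomes. Analysis of covariance appears only later, as one of three options for the endocannabinoid data.

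The sample size (Participants) is "30 patients in the experimental group and 30 patients in the control group", derived for a comparison "using a bilateral Student’s *t* test for two independent samples". The article gives no effect size, standard deviation or within-patient correlation, and it does not link this calculation to the clinical and functional outcomes.

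**The concern.** The baseline visit precedes treatment, so no treatment effect can exist there. A repeated measures model that treats it as an ordinary outcome level offers two between-arm tests by default, and neither is a good match for objective 2.

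- **Group main effect.** It compares the five-visit averages. One of the five carries no effect, so a benefit that is constant after treatment is shrunk by one fifth. The baseline measurement is also not used to reduce variance.
- **Group-by-time.** It asks whether the two profiles are parallel. It has 4 degrees of freedom, takes no account of direction and yields no single effect with a confidence interval.

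The two tests can disagree, and the article does not say which one decides. In a trial of 60 patients, a real benefit on PANSS, FAST or the mood and anxiety scales could be missed, or could be understated if the main effect were reported as the treatment effect.

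**Working it through.** **The plan's own figure.** With no effect size given, 30 per arm cannot be derived forward. Solving backwards (two-sided 5%, 80% power, 30 per arm, noncentral t) gives d = 0.736, and that d returns 30 per arm. The sample size is therefore possible, but it says nothing about these outcomes.

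**Inputs.** From the article: n = 30 per arm, two-sided 5%, five visits. Assumed here: unit variance, equal correlation ρ between all visits, no dropout, no expected baseline difference, and a constant effect δ = 0.5 SD at the four later visits.

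**Formulas.**
- Group main effect: mean effect (0 + 4δ)/5 = 0.8δ = 0.40 SD. The variance of a five-visit mean is (1 + 4ρ)/5. Test statistic: 0.40 / √(2·(1 + 4ρ)/5 / 30).
- Group-by-time: F with 4 and 232 df. The noncentrality is (30/2)·Σ(δₜ − mean)²/(1 − ρ). The sum is 0.4² + 4·0.1² = 0.20, so the noncentrality is 3/(1 − ρ).
- Mean of the four post-baseline visits, adjusted for baseline: residual variance (1 + 3ρ)/4 − ρ². Test statistic: 0.50 / √(2·residual variance/30).

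**At ρ = 0.5.** Main effect: 0.40/√(2·0.6/30) = 2.00. Group-by-time noncentrality: 6. Adjusted mean: 0.50/√(2·0.375/30) = 3.16.

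**Power, constant 0.5-SD effect.**

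| ρ | Group main effect | Group-by-time | Adjusted mean | Loss of the better planned test |
|---|---|---|---|---|
| 0.3 | 63% | 34% | 87% | 23 points |
| 0.5 | 50% | 46% | 87% | 37 points |
| 0.7 | 42% | 71% | 95% | 24 points |

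Losses are taken before rounding. A simulation of 4,000 trials per scenario gave 64/34/86%, 50/47/87% and 41/71/94%, that is, losses of 22, 37 and 23 points. With no effect, all three tests rejected in 4.4% to 5.3% of simulated trials.

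**How far this depends on the assumptions** (equal correlation):
- *Fading effect (0.7, 0.53, 0.35, 0.18 SD).* Simulated power for main effect, group-by-time and adjusted mean: 39/66/77% at ρ = 0.5 and 33/90/87% at ρ = 0.7. Group-by-time loses 11 points in the first case and nothing in the second.
- *Constant effect of 0.736 SD.* The adjusted mean has 99.5% to 99.9% power. The main effect loses 7.3, 17.1 and 27.0 points at ρ = 0.3, 0.5 and 0.7; group-by-time loses 32.7, 16.8 and 2.6. The better test loses 7.3, 16.8 and 2.6.
- *Effect growing to 0.736 SD at 1 year.* At ρ = 0.5: adjusted mean 81.6%, main effect 44.0%, group-by-time 71.3%. At ρ = 0.7: adjusted mean 90.6%, group-by-time 92.2%.
- *Correlation decaying with time (first-order autoregressive, ρ 0.2 to 0.5), constant effect set to give the adjusted mean 80% power.* The main effect loses 10.7 to 17.4 points.

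The dilution to 4/5 of a sustained effect needs none of these assumptions beyond a constant post-baseline effect.

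**The case against.** The strongest defence has four parts.

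1. **Group-by-time does address objective 2.** The objective speaks of reduced symptoms and improved functioning, which are changes from baseline. Randomisation makes the expected baseline difference zero, so the null of parallel profiles is the same as no arm difference at any later visit. This stands. A reader might infer that neither test bears on the follow-up difference; the documents do not support that. What remains is inefficiency and the lack of a single estimate.
2. **The power loss has no fixed floor.** A reader might take 20 points as a minimum. That also fails: effect size, correlation and effect shape are all assumed, and several plausible combinations give smaller losses or none.
3. **Baseline as a level is not wrong in itself.** A model with baseline means constrained equal across arms also keeps baseline in the outcome vector, and contrasts can be drawn from any repeated measures model. True, but the article states neither the constraint nor a contrast. A contrast of post-baseline mean minus baseline without the constraint would still be inefficient: at ρ = 0.5 its variance is 0.625 + 1 − 2·0.5 = 0.625 against 0.375, so the statistic is 0.5/√(2·0.625/30) = 2.45 rather than 3.16.
4. **A condensed article may leave covariates and contrasts to a fuller document.** This limits the point. The article does not say that the main effect will be reported as the treatment effect, so the 20% understatement is conditional. But the article does commit to a model family and to its five levels, and that stated choice is what should change.

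These are also secondary outcomes, for which the 60 patients were not calculated.

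**Conclusion.** The point holds as an improvement to a stated analysis, not as an invalid test. Baseline is listed as an outcome level, with no adjustment and no named contrast. The group main effect then estimates 4/5 of a sustained benefit, and group-by-time is valid but is an undirected 4-df test without a treatment estimate. With 30 per arm, a constant 0.5-SD effect, equal correlation of 0.3 to 0.7 and no dropout, the better of the two loses about 22 to 37 points of power against the baseline-adjusted post-baseline mean. Under other assumptions the loss is smaller, and for fading or growing effects at correlation 0.7 it disappears. The documents do not settle which case applies, so no general figure for the loss should be quoted. The change is worth making because it is free; its weight is limited by the secondary status of these outcomes.

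**What to change.** For the continuous clinical and functional outcomes, replace the sentence in the Statistical analysis section with text such as:

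*Each continuous clinical and functional outcome will be analysed with a mixed model whose outcome vector is post-treatment, 3 months, 6 months and 1 year. The baseline value of that outcome is a covariate; arm, visit and arm-by-visit are fixed effects. Objective 2 is tested by the arm difference averaged over the four post-baseline visits. Visit-specific differences are reported with 95% confidence intervals.*

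Keeping baseline in the outcome vector with its mean constrained equal in both arms is an acceptable alternative, provided that the constraint and the contrast are written down.

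The cost is wording only. The baseline values are already collected, the visits are unchanged, the model runs in the SPSS version already named, and no further patients or procedures are needed.
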